
### 2.2. Experimental Vignettes

The four vignettes describe distinct configurations of AI involvement in facial reconstructive surgical planning, varying both the AI’s task (imaging analysis, decision support, outcome simulation, autonomous planning) and the surgeon’s level of supervision (Table 1). Each configuration corresponds to a capability documented in the current literature: anatomical structure analysis from CT [6,8], algorithmic generation of candidate surgical plans [9], three-dimensional simulation of postoperative facial appearance [12,13], and highly autonomous planning of the kind anticipated by surgical-autonomy frameworks [14,15]. All vignettes open with an identical premise (the respondent needs facial reconstructive surgery following an injury) and are written in parallel second-person wording of comparable length and reading difficulty, so that scenario content—not framing—drives differences in responses. Because the four configurations differ in what the AI does as well as in how much the surgeon decides, a perceived difference between them could in principle reflect technical sophistication rather than autonomy. Three features are intended to keep the two apart. First, every vignette closes by stating explicitly how the final surgical plan is reached and by whom. In Scenarios A–C, a single clause of parallel construction names the surgeon as the decision-maker (making all decisions, choosing among the proposed options, or deciding the final plan after reviewing the simulations); in Scenario D, the closing sentences state that the surgeon reviews the AI’s plan but rarely modifies it. What varies is therefore the decisional locus, not the computational task. Each comprehension check is built on that same feature: the decision-maker in Scenarios A and B; the role of the system in Scenario C (whose decisional clause is functionally equivalent to Scenario B’s, so that the role is what distinguishes the two); and the origin of the plan actually followed in Scenario D. Second, the vignettes are matched on the quantity of technical detail supplied—one sentence describing the system’s input and output in each case—so that described sophistication does not rise in step with autonomy. Scenario C specifies a generative three-dimensional simulation, computationally the most elaborate output in the set, yet leaves the decision entirely with the surgeon; Scenario D describes a comparatively conventional optimization whose distinguishing feature is decisional rather than technical. Third, two manipulation checks follow every scenario: MAN1, perceived control of the AI over the final decision, and MAN2, perceived technical sophistication of the system. The manipulation is treated as valid only if MAN1 orders the scenarios as intended; MAN2 verifies that sophistication does not itself increase monotonically with autonomy and enters a pre-specified sensitivity analysis as a covariate, so that the autonomy effect can be estimated with perceived sophistication held constant (Section 2.9.1). The full vignette texts are provided in Appendix A.

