### 2.5. Sample Size and Power

Sample size is justified a priori following current recommendations [70], with all calculations derived analytically from noncentral *F*, t, and chi-square distributions at a two-tailed significance threshold of α = 0.05 and a target power of 1 − β = 0.80, reproducible in G*Power 3.1 (“ANOVA: Repeated measures, within factors”) and consistent with recent tutorials on power analysis for repeated-measures designs [63]. The primary test is a repeated-measures ANOVA (four within-subject levels) on each composite score. Assuming a correlation between repeated measurements of ρ = 0.50 (a typical value for repeated attitudinal ratings, to be verified in the pilot), the minimum sample is 24 participants for medium effects (*f* = 0.25) and 138 for small effects (*f* = 0.10); under the conservative assumption ρ = 0.30, these become 32 and 193, respectively. The minimum analyzable threshold is therefore set at *N* = 140 valid participants, sufficient to detect even small between-scenario effects under realistic conditions. Because these thresholds depend on ρ, an adaptive rule is pre-registered for the case in which the pilot estimate falls outside the assumed ρ = 0.30–0.50 range. The pilot returns $\hat{\rho }$ with a 95% confidence interval, and every threshold is recomputed at its lower bound, ρ_L_, which is the conservative choice. The number of valid participants required to detect *f* = 0.10 at power 0.80 is 274, 247, 220, 193, 165, and 138 for ρ_L_ = 0, 0.10, 0.20, 0.30, 0.40, and 0.50, respectively; an intermediate ρ_L_ is rounded down to the nearest tabulated value, so that the rule is fully determined in advance for any estimate the pilot can return. Two consequences follow. The recruitment target does not change because the requirement is a decreasing function of ρ and reaches only 274 in the theoretical worst case of ρ_L_ = 0; *N* = 300 preserves power ≥0.80 against small between-scenario effects for every value ρ can take, and the target is in any case set by the person-level analyses described below, which do not depend on ρ. The analytic floor does change: it is redefined as the value tabulated above for the observed ρ_L_, so that it remains at the pre-specified *N* = 140—rounded up from 138—only when ρ_L_ ≥ 0.50 and rises to 165, 193, 220, 247, or 274 as ρ_L_ falls to 0.40, 0.30, 0.20, 0.10, or 0. A ρ_L_ below 0.10 would in addition indicate that the composites are unstable across repetitions rather than that participants are inconsistent, and would therefore also trigger re-inspection of pilot reliability and of the measurement-invariance assumptions before the main study is launched. Any application of this rule, and the $\hat{\rho }$ that triggered it, will be recorded in the pre-registration and reported in the results article.

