
The recruitment target is *N* = 300 valid participants. This target is dictated not by the within-subjects effects (for which power at *N* = 300 is 0.99 for small effects at ρ = 0.50, with a minimum detectable effect of *f* = 0.07), but by the person-level analyses: the familiarity moderation (minimum detectable interaction *f*^2^ = 0.037 at *N* = 300), the global preference test (minimum detectable *w* = 0.21 on 5 degrees of freedom), and descriptive analyses of demographic subgroups. A small interaction effect (*f*^2^ = 0.02) would require *N* ≈ 550; H4 therefore remains partially exploratory, and a non-significant result will not be interpreted as evidence of absence. At *N* = 300, dependent pairwise comparisons detect differences from *dz* = 0.16 (uncorrected) and *dz* = 0.20 (at the Bonferroni bound for six pairwise comparisons), so all six scenario contrasts can be treated as confirmatory. Counterbalancing entails no loss of sensitivity for the primary comparisons: with sequence entered as a four-level between-subjects factor, the autonomy main effect retains 3 degrees of freedom and the same noncentrality, so the minimum detectable effect at *N* = 300 remains *f* = 0.07. The scenario × sequence interaction—the direct test of order dependence—carries 9 degrees of freedom and a minimum detectable effect of *f* = 0.08 at ρ = 0.50 (*f* = 0.10 at ρ = 0.30), giving power of 0.95 against a small order effect of *f* = 0.10; the serial-position main effect in the additive model carries 3 degrees of freedom and matches the sensitivity of the autonomy effect itself. Order artifacts large enough to masquerade as the hypothesized autonomy gradient are therefore detectable, rather than being assumed away. In the pilot, by contrast, the ascending and descending arms (*n* = 25 each) bound order effects only at *f* = 0.17, which excludes medium-to-large artifacts but not small ones; the definitive test is the main-study interaction. Table 2 summarizes the power analysis, and Figure 1 shows achieved power as a function of the number of valid responses.

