
### 2.9. Statistical Analysis

#### 2.9.1. Primary Analyses

Each composite score (acceptability, trust, perceived risk) will be analyzed by a mixed repeated-measures ANOVA, with autonomy level (four scenarios) as the within-subjects factor and presentation sequence (four Williams sequences) as the between-subjects factor. The Greenhouse–Geisser correction will be applied when Mauchly’s test indicates a sphericity violation (Huynh–Feldt for ε between 0.75 and 1), and the multivariate approach (Pillai’s criterion) will be reported in parallel as a sphericity-robust check. H1 and H2 will be tested with within-subjects trend contrasts across the autonomy gradient. Because acceptance need not fall in a straight line, the complete set of orthogonal polynomial contrasts—linear, quadratic, and cubic—is pre-specified, and each is reported together with the proportion of the omnibus effect it accounts for. A purely linear profile leaves the quadratic and cubic components negligible, whereas a step between two adjacent levels appears as a large linear component accompanied by a substantial quadratic or cubic one. Because every monotone step is linear-dominant, the polynomial decomposition establishes departure from a straight line but cannot by itself locate the break; the break is identified only from the Holm-corrected adjacent-pair contrasts (A–B, B–C, C–D). A quadratic-dominant profile with a small linear component would instead indicate a non-monotone pattern, which the hypotheses do not predict and which would be reported as such. A non-monotonic or threshold pattern will be reported as such rather than summarized by the linear trend alone. Post hoc comparisons use dependent-samples *t*-tests for the six scenario pairs with Holm’s sequential correction, applied within each hypothesis-defined family of tests in line with current guidance on multiplicity control [74]. Effect sizes will be reported as partial η^2^ for omnibus tests and Cohen’s dz for pairwise comparisons, with 95% confidence intervals, following effect-size-centered reporting recommendations [64]. Assumption checks include graphical inspection of difference-score distributions; as a distributional robustness analysis, the Friedman test with Holm-corrected Wilcoxon signed-rank pairwise comparisons will be reported alongside each primary test—supplemented by ordinal (cumulative-link) models as sensitivity analyses for the Likert-based outcomes [71]—and the concordance of parametric and nonparametric conclusions stated explicitly. Order dependence is tested directly as the scenario × sequence interaction; a non-significant interaction, together with equivalence of the four sequence-specific profiles, supports pooling across sequences. Independently of that test, the autonomy effect is re-estimated from a linear mixed model with random intercepts per participant and additive fixed effects of autonomy level and serial position (1–4). The Williams square renders this model identified, so the estimate is adjusted for arbitrary—not merely linear—serial-position and fatigue effects, while first-order carry-over is balanced by the design rather than modeled; position-adjusted and unadjusted estimates are reported side by side, and any material divergence between them is treated as evidence of an order artifact and interpreted accordingly. Perceived difficulty (DIF1) and perceived technical sophistication (MAN2) are each added as time-varying covariates in further sensitivity models, addressing fatigue and the possibility that responses track the apparent complexity of the system rather than its autonomy. Finally, between-person heterogeneity in response profiles is examined by adding a random slope for the linear autonomy contrast and testing the improvement in fit by a likelihood-ratio test; a substantial random-slope variance indicates that an average trajectory conceals distinct response patterns and licenses the exploratory typology described in Section 2.9.2. Because a non-significant test is not evidence of absence, a smallest effect size of interest of *dz* = 0.20—the value detectable at the Bonferroni bound for the six pairwise contrasts at *N* = 300—is fixed in advance, and equivalence testing by two one-sided tests against that bound is reported alongside every null pairwise result, so that any claim that two adjacent scenarios do not differ rests on an equivalence test rather than on the absence of significance.

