H4. moderation by AI familiarity (partially exploratory)	RM-ANCOVA or linear mixed model with random intercepts: scenario (within) × B1 (centered), sequence between	F (or likelihood-ratio test), *p*, *f*^2^; simple slopes with 95% CI
Global preference (P1)	Goodness-of-fit chi-square over 6 analysis categories (2 undecided options pooled); standardized residuals; consistency with maximum-acceptability scenario, descriptive	χ^2^, *df*, *p*, *w*; standardized residuals
Predictors of acceptability	Person-level multiple regression: mean acceptability on familiarity, general attitudes, demographics	*B*, *SE*, β, 95% CI, R^2^, VIF
P2, P4a/P4b (exploratory)	Brief thematic analysis (P2); descriptive statistics, within-person P4a–P4b difference, and correlations with RES5/RES6	Theme frequencies; Pearson/Spearman *r*
Order dependence (design validation)	Scenario × sequence interaction in the mixed RM-ANOVA; position-adjusted linear mixed model (autonomy + serial position, random intercepts)	*F*, corrected *df*, *p*, partial η^2^ (90% CI); adjusted vs. unadjusted scenario means
Functional form of the autonomy effect	Orthogonal polynomial contrasts (linear, quadratic, cubic); Holm-corrected adjacent-pair contrasts	*F*, *p*, partial η^2^ per contrast; share of the omnibus effect
Autonomy vs. technical complexity	Mixed RM-ANOVA on MAN2 (sequence between); primary models re-estimated with MAN2 as a time-varying covariate	*F*, corrected *df*, *p*, partial η^2^; adjusted scenario means
Between-person heterogeneity (exploratory)	Random-slope linear mixed model; latent-class growth analysis of individual trajectories	Likelihood-ratio χ^2^, *p*; random-slope SD; class sizes, BIC, entropy

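### The sophistication-adjusted sensitivity model does not separate within-person from between-person variation in MAN2, so its autonomy contrast can be biased when scenarios differ in rated sophistication

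*Protocol article*

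**What the plan says.** Section 2.9.1 re-estimates the autonomy effect in a linear mixed model with a random intercept per participant and additive terms for autonomy level and serial position. It then adds: "Perceived difficulty (DIF1) and perceived technical sophistication (MAN2) are each added as time-varying covariates in further sensitivity models". Table 5 describes the MAN2 analysis as "primary models re-estimated with MAN2 as a time-varying covariate". Section 2.2 states the purpose, "so that the autonomy effect can be estimated with perceived sophistication held constant".

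Three further points matter:

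- Section 2.2 describes Scenario C as having the most elaborate output and Scenario D as comparatively conventional, so unequal MAN2 means are plausible by design.
- The pilot criterion in Section 2.8(v) rules out only a monotone rise of MAN2 with autonomy. It does not require equal means.
- Centering is mentioned only for B1, a person-level moderator. Nothing is said about how MAN2 or DIF1 is parameterised.

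**The concern.** The autonomy contrast is a within-person comparison, so the only MAN2 slope that belongs in its adjustment is the within-person one: how a participant's outcome moves when that same participant rates a system as more sophisticated. A random-intercept model with one undivided MAN2 term estimates a weighted mix of that slope and the between-person slope, which reflects whether people who rate every system as more sophisticated also accept AI more readily. The mixed slope is then multiplied by the MAN2 difference between scenarios and removed from the autonomy contrast. If general enthusiasm for AI drives both ratings, the adjusted contrast moves although neither autonomy nor sophistication has an effect within persons.

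At stake is the model-based answer to a rival explanation that the protocol itself raises: that responses follow the apparent complexity of the system rather than its autonomy.

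**Working it through.** **Inputs from the protocol (Section 2.5).** "two-tailed significance threshold of α = 0.05 and a target power of 1 − β = 0.80"; "Assuming a correlation between repeated measurements of ρ = 0.50"; the alternative "under the conservative assumption ρ = 0.30"; and "The recruitment target is *N* = 300 valid participants". The design has m = 4 ratings per person.

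**The plan's own figures reproduce.** With λ = f²·N·m/(1−ρ) and degrees of freedom 3 and 3(N−1):

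- ρ = 0.50, N = 138: λ = 0.01 × 138 × 4 / 0.50 = 11.04, and power reaches 0.80 at this N.
- ρ = 0.30, N = 193: λ = 0.01 × 193 × 4 / 0.70 = 11.03, again 0.80.
- Pairwise bound at N = 300: (1.960 + 0.842)/√300 = 0.162; at α = 0.05/6, (2.638 + 0.842)/√300 = 0.201.

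The protocol gives no figure for the covariate-adjusted models, so what follows rests on stated assumptions.

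**Weight of the between-person slope.** Take both variables with SD 1 and intraclass correlation 0.50 (the plan's ρ for the outcome, an assumption for MAN2).

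- Random-intercept weighting multiplies between-person information by 0.5/(0.5 + 4 × 0.5) = 0.2.
- Between-person information on MAN2: (1 + 3 × 0.5) × 0.2 = 0.5. Within-person: 3 × 0.5 = 1.5.
- Weight on the between-person slope: 0.5/(0.5 + 1.5) = 0.25.

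**Size of the spurious slope.** Assume a person-level correlation of 0.5 and a within-person slope of 0.

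- Slope of the person-mean outcome on person-mean MAN2: (0.5 × 0.5)/(0.5 + 0.5/4) = 0.25/0.625 = 0.40.
- Fitted slope: about 0.25 × 0.40 = 0.10. Simulation gives 0.11; the true value is 0.

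**Bias of a contrast** = −(fitted slope − within-person slope) × (MAN2 difference). With slope 0.11, and MAN2 means for A/B/C/D in SD units:

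- 1 SD monotone rise: D−A = −0.11.
- 0/0.4/1.0/0.7: D−A = −0.11 × 0.7 = −0.08; D−C = −0.11 × (−0.3) = +0.03.
- 0/0.4/0.8/0.2: D−A = −0.02; D−C = +0.07.

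At ρ = 0.50 the difference of two ratings has SD √(2 × 0.5) = 1, so these values are also on the dz scale and lie below the plan's 0.20 bound.

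**Rejection rates** (simulated: N = 300, four Williams sequences, position in the model, no true autonomy effect, no within-person MAN2 slope):

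| MAN2 profile, person-level correlation 0.5 | One MAN2 term, 3-df test | Mean + deviation |
|---|---|---|
| 1 SD monotone rise | about 28% | about 5% |
| C-peaked profiles | about 19–27% | 4–6% |

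For 0/0.4/1.0/0.7, the rate is 13%, 27% and 55% at correlations 0.3, 0.5 and 0.7.

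A separate set of assumptions used a MAN2 SD of 1.4 points, a between-person slope of 0.4 and means of 0/0.5/1/0.5 points (a peak of 1/1.4 = 0.71 SD). It gave 11% at outcome correlation 0.50 and 16% at 0.30. The mean-plus-deviation entry returned 4.3–5.4% across the key settings of that set.

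**When nothing happens.** With equal MAN2 means, or equal within- and between-person slopes, rejection stayed at about 4–6%.

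**Limit of the split.** These rates treat MAN2 as error-free. With an assumed single-item reliability of 0.6 and a real within-person slope, neither entry restores 5%, and the split can do worse: 41% against 23% in one setting and 46% against 34% in another.

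**The case against.** The strongest reply is that the article never says MAN2 enters undivided. A separate statistical analysis plan is to be deposited with the pre-registration and could fix the parameterisation. Table 5 also speaks of the primary models, which are mixed repeated-measures ANOVAs; a covariate fitted in the within-subject stratum would use only the within-person slope and would not leak. Both points stand as limits. However, Section 2.9.1 places the covariates directly after the random-intercept model, and Section 2.2 already attaches a conclusion that depends on the choice. The ordinary reading is one term with one slope.

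A reader might infer that the check is tilted towards confirming H1. The documents do not support that. A sizeable monotone rise from A to D, which would tilt it that way for acceptability, is what the pilot criterion is meant to catch. Where C is rated above D, as the vignettes suggest, the bias in D−C is positive and works against the drop in acceptability that the authors expect there.

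It is also fair that the larger rejection rates assume a within-person slope of exactly zero, and that the bias disappears as the two slopes converge. For DIF1 the mechanism is the same but was not simulated. Fatigue follows serial position, which the Williams square makes orthogonal to scenario, so only genuine scenario differences in difficulty could leak.

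**Conclusion.** The point holds as a cheap and worthwhile correction to a sensitivity analysis. On the ordinary reading, the MAN2-adjusted autonomy contrast is biased when two conditions hold together: scenario means of MAN2 differ, and the between-person slope differs from the within-person slope. The first is plausible from the protocol's own vignette design; the second is an assumption. At person-level correlation 0.5, MAN2 intraclass correlation 0.5 and no within-person slope, the 3-df test rejects about 19–27% of the time for C-peaked profiles and about 28% for a 1 SD monotone rise, with point bias of roughly 0.02–0.11 SD in a direction set by the profile. Smaller MAN2 differences or a lower correlation bring the rates down.

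It would go too far to conclude that the H1 or H2 results are compromised. The primary ANOVAs contain no MAN2 or DIF1 term, and no decision rule is tied to these sensitivity models. Nor does the split make sophistication truly constant, because MAN2 is a single item measured with error.

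**What to change.** In Section 2.9.1 and in the Table 5 row on autonomy versus technical complexity:

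- Name the random-intercept mixed model (autonomy level plus serial position) as the host for the covariate-adjusted analyses.
- Enter MAN2 as two terms, the participant's mean over the four scenarios and the deviation from that mean, and report scenario means adjusted for the deviation.
- Treat DIF1 the same way where its scenario means differ.
- In Section 2.2 and in reporting, describe the result as adjusted for rated sophistication, and state that measurement error in a single item leaves residual confounding.

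The cost is one extra fixed effect per covariate, a slightly wider interval for the adjusted contrast, and a line or two of text and code. No new data are needed, and the pre-registration has not yet been filed.
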